### Outcomes

Data collection points are outlined in table 2.

**Table 2 T2:** Data collection time points

	Baseline/randomisation (day 0)	Daily until symptom resolution	Weekly (days 7, 14, 21, 28)	Symptom resolution	Symptom deterioration*	During hospitalisation	Day 90	13.5 months
Data collected by site staff								
Demographics and medical history (including medication to prevent OHSS)	OPt							
Symptoms: Fluid balance including fluid drunk, urine output‡ Diarrhoea and vomiting Nausea§ Abdominal girth Pain Shortness of breath Weight	OPt	SR	T/OP†	OPt	OPt	IP/MN		
Blood tests (FBC)—if a face-to-face appointment	OPt		T/OP†	OPt	OPt	IP/MN		
Training and provision of consumables, and record details	OPt							
EQ-5D-5L questionnaire	OPt	SR				SR/IP		
OHSS-related hospital admission within 28 days (primary outcome) and reasons for hospitalisation			T/OPt	OPt	OPt			
Intervention delivery (volume of ascites removed, number of paracentesis)			MN	OPt		MN		
Conservative management arm—details of usual care monitoring			MN	OPt				
Use of GnRH antagonist for treatment of OHSS			OPt	OPt	OPt	IP/MN		
Confirmation of symptom resolution				OPt		MN		
Adverse events (patient)		T¶	OPt / MN	OPt	OPt	IP		
Pregnancy outcome (eg, miscarriage) and ongoing pregnancies							MN	
Incidence of thrombosis or embolism or significant infection							MN	
Live birth information and pregnancy outcome (eg, miscarriage)								MN
Neonatal death and SAEs related to the baby								MN
Data collected by the central study team								
Health resource use questionnaire			Q (day 28 only)					
CSQ-8 questionnaire			Q (day 28 only)					
Patient cost questionnaire			Q (day 28 only)					
EQ-5D-5L questionnaire			Q (day 28 only)					

*If symptoms deteriorate to the point where hospital admission is thought to be required.

†If OHSS symptoms have not resolved by this time point.

‡Fluid balance will be self report throughout.

§Nausea will not be collected as part of the daily patient diary.

¶This will only be possible for participants who are being contacted daily. When they are not being contacted daily it will be asked at every contact.

CSQ-8, Client Satisfaction Questionnaire 8; FBC, full blood count; IP, inpatient; MN, medical notes; OHSS, ovarian hyperstimulation syndrome; Opt, outpatient; Q, data collected via a questionnaire; SAE, serious adverse event; SR, self-reported by the patient; T, data collected over the telephone by a research nurse.

Primary outcome is any:

OHSS-related hospitalisation for at least 24 hours within 28 days of randomisation.

Secondary outcomes:

Need for OHSS-related hospitalisation within 28 days—independent blinded central assessment.Time to resolution of OHSS assessed within 28 days of randomisation.Progression of OHSS severity within 28 days of randomisation.Cumulative length of OHSS-related hospitalisation.Live birth, pregnancy outcomes, neonatal death and serious adverse events (SAEs) including congenital abnormalities in the new-born within 13.5 months of randomisation.The occurrence of thrombosis, embolism and significant infections requiring antibiotic treatment or hospitalisation within 90 days of randomisation.AEs within 28 days of randomisation.Patient satisfaction assessed using the Client Satisfaction Questionnaire 8^19^ based on total scores at 28 days postrandomisation.EQ-5D-5L participant quality of life daily and at 28 days postrandomisation.Health resource use and patient costs at 28 days postrandomisation.

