### Intervention and control

Following randomisation, women in the intervention arm will have OP performed in the outpatient setting as soon as clinically possible. Sites will follow their own local procedures for conducting paracentesis either abdominally or vaginally by a suitably trained doctor, advanced nurse practitioner or radiologist in the fertility, gynaecology or radiology unit and while the trial does not dictate how to perform the intervention, guidance will be offered.

If rehydration is required via intravenous methods, this will be at the discretion of the attending clinician. If a large volume of fluid is removed, then intravenous colloid therapy should be considered. If this administration of fluid results in overnight inpatient hospitalisation it will not be viewed as meeting the trials primary outcome relating to hospitalisation. Some patients may require multiple drainage which can be performed if the participant has a reaccumulation of ascites.

Women in the UC group will not have the paracentesis performed in an OP setting and will be monitored by their clinical team as per UC. If UC at the site involves administering paracentesis on an outpatient basis for treatment of OHSS then the site will be requested to stop routinely providing this for participants in the UC arm.

Both groups of women will be provided with access to a diary (either in paper format or sent electronically using Research Electronic Data Capture (REDCap)^18^ hosted at The University of Sheffield for the purpose of daily self-report of weight, abdominal girth, diarrhoea, vomiting, pain, shortness of breath, fluid input and urine output. This information will be used by the clinical team in the intervention arm on a daily basis to inform further management and whether to perform further OP. The UC group will also perform daily self-monitoring, but these data will be sent directly to CTRU for input into the database and will not be available to be reviewed by site staff.

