### Blinding

It will not be possible to blind participants or clinicians to treatment allocation. The trial statistician and TSC will be blinded. To assess the potential impact of outcome assessment bias, an additional analysis of the primary endpoint will be performed, using an independent blinded adjudicated primary outcome concerning whether trial participants needed OHSS-related hospitalisation within 28 days.

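### Every listed admission outcome is restricted to OHSS-related stays, so an admission for a paracentesis complication can go uncounted; a supportive all-cause comparison by randomised arm would close the gap cheaply

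*Protocol article*

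**What the plan says.** The Outcomes section of the protocol article defines the primary event as any "OHSS-related hospitalisation for at least 24 hours within 28 days of randomisation". Two secondary outcomes also concern hospital stay, and both are limited by cause: "Need for OHSS-related hospitalisation within 28 days—independent blinded central assessment" and "Cumulative length of OHSS-related hospitalisation".

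Table 2 lists, among the data collected by site staff, "OHSS-related hospital admission within 28 days (primary outcome) and reasons for hospitalisation". The Blinding section states that "It will not be possible to blind participants or clinicians to treatment allocation". It adds a further analysis of the primary endpoint based on "an independent blinded adjudicated primary outcome concerning whether trial participants needed OHSS-related hospitalisation within 28 days".

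The Intervention and control section deals with one kind of treatment-related stay. On intravenous fluid, which it suggests considering after large-volume drainage, it says: "If this administration of fluid results in overnight inpatient hospitalisation it will not be viewed as meeting the trials primary outcome relating to hospitalisation". It does not say how an admission for any other consequence of the procedure is to be classified.

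Complications are captured elsewhere. All adverse events are recorded in both arms, and the secondary outcomes include thrombosis, embolism and "significant infections requiring antibiotic treatment or hospitalisation within 90 days of randomisation". The Statistical analysis section says safety outcomes will be summarised descriptively in a treatment-as-received population.

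**The concern.** OP is an invasive procedure and may be repeated. If it causes an admission, for example for infection, the cause is the treatment and not necessarily OHSS. On the wording of the primary outcome, that woman can be scored as not hospitalised. The usual-care arm has no outpatient paracentesis, and a usual-care woman drained as an inpatient has normally been admitted already. Admissions of this kind would therefore arise almost only under OP.

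Cause is also a judgement, made first by people who know the allocation. An uncertain admission after a drain can be put down to OHSS or to something else, and that choice decides whether it counts.

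At stake is how the result can be read. A lower rate of OHSS-related admission is the trial's stated objective. Commissioners and patients will also want to know whether OP keeps women out of hospital, and the planned economic result is a cost per hospitalisation avoided. The same endpoint also drives the interim futility decision.

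**Working it through.** **1. Which outcomes could pick up a procedure-related admission of 24 hours or more?**

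| Outcome or data item | Restricted to OHSS-related? | Compared by randomised arm? |
|---|---|---|
| Primary outcome | Yes | Yes |
| Blinded assessment of need | Yes | Yes |
| Cumulative length of stay | Yes | Yes |
| Infection, thrombosis, embolism to 90 days | No, but only these causes, and infection also counts if treated with antibiotics alone | Method not stated in the article |
| Adverse events and serious adverse events | No | Descriptive, by treatment received |
| Health resource use | Not stated | Enters as costs, not as an admission rate |

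No row gives the proportion of each randomised arm with any admission of at least 24 hours.

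**2. Does the plan's own design reproduce?** Inputs from Sample size and interim analyses: 41% under usual care, 20-point reduction (so 21% under OP), one-sided 2.5%, interim at 73 per arm, maximum 112 per arm, stop if the observed reduction is below 4.5 points. The final test is taken as z = (p_UC − p_OP) / √(2p̄(1 − p̄)/112), rejecting at z ≥ 1.96.

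- Fixed-design size with pooled variance: 111 per arm, against 112 stated.
- Power by a two-stage normal calculation: 90.2%, against 90% stated.
- Futility stop under 41% v 21%: 1.9% by the normal calculation, as stated.
- Futility stop under 41% v 41%: 72.2% by exact binomial enumeration, as stated (71.0% by the normal calculation).
- One-sided error under 41% v 41%, exact: 2.4%.

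The design figures are sound.

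**3. How sensitive is the design to classification?** The article gives no rate for procedure-related or other non-OHSS admissions, so the shift below is an assumption. True admission is 41% in both arms. Some OP admissions that would have counted are instead classed as not OHSS-related. The same exact enumeration gives:

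| Shift in OP arm | Apparent OP rate | Superiority declared | Futility stop |
|---|---|---|---|
| 0 points | 41% | 2.4% | 72% |
| 2 points | 39% | 4.7% | 63% |
| 4 points | 37% | 8.6% | 54% |
| 5 points | 36% | 11.3% | 49% |

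**4. When does this not apply?** If OHSS-related admission is 41% in both arms and complication admissions come on top, the counted OP rate stays at 41% and the error stays at 2.4%. The inflation in step 3 needs uncounted admissions to replace counted ones.

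**5. What would an all-cause analysis cost in power?** Add an independent background admission rate b to both arms: p = 1 − (1 − p_OHSS)(1 − b).

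- b = 2%: 1 − 0.59 × 0.98 = 42.2% v 1 − 0.79 × 0.98 = 22.6%. The difference is 19.6 points and power is 88%.
- b = 5%: 1 − 0.59 × 0.95 = 44.0% v 1 − 0.79 × 0.95 = 25.0%. The difference is 19.0 points and power is 85%.
- If OP itself adds 5 points of admissions (41% v 26%), power is 66%. That loss reflects a smaller real benefit, which is what the analysis is meant to show.

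**The case against.** The strongest reply is that the endpoint is deliberate and coherent. The primary objective is the rate of OHSS-related admission, the 26/63 audit behind the 41% measures the same thing, and procedural harm is conventionally reported as safety. All of that stands, and it is why the primary outcome should not be redefined in a trial that has been recruiting since June 2022.

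Blinded adjudication is a real safeguard against biased labelling. It answers much of the worry about unblinded attribution, but not all of it. It is a secondary and additional analysis, and the article does not say whether adjudicators see every admission or only those that sites label OHSS-related. An adjudicator who correctly attributes an admission to the procedure would still have no OHSS-related event to record.

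A reader might infer that the protocol excludes admissions for paracentesis complications. It does not say so. The only stated exclusion is the fluid-related overnight stay, and the need to state that one could suggest that other treatment-related stays do count. The fair reading is that their classification is left open. A reader might equally take the 4.7–11.3% as the trial's actual error rate. Step 4 shows why not: the figures need one-for-one replacement, and the documents supply no rate.

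Finally, the statistical analysis plan and full protocol are not shown and may already contain an all-cause analysis. The statement here is about the article only.

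**Conclusion.** The point holds as a cheap improvement. It is not an error or a contradiction in the plan. The listed hospitalisation outcomes are all cause-restricted, cause is first assigned without blinding, and adjudication keeps the restriction. An admission caused by paracentesis can therefore go uncounted, and the article states no randomised comparison that would reveal it. Descriptive safety tables by treatment received do not fill the gap, because usual-care women drained in hospital could be grouped with OP.

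The size of any bias is unknown. On the assumption of a 2 to 5 point reclassification in the OP arm, with true rates of 41% in both, the one-sided error would be 4.7% to 11.3% instead of 2.4%. With purely additional complication admissions it would not move. The documents do not support the stronger conclusions that the primary outcome is invalid or that harms are concealed.

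**What to change.** Keep the primary outcome as it is. In the statistical analysis plan, before unblinded data are accessed:

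- Add a supportive intention-to-treat analysis of all-cause admission of at least 24 hours within 28 days, with the risk difference and 95% CI reported beside the primary result. Fluid-related stays that reach 24 hours would count in this analysis only.
- State how admissions for complications of paracentesis are classified for the primary outcome, alongside the existing rule on fluid-related stays.
- Have the blinded adjudicators review every admission record, not only those labelled OHSS-related by sites.

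The analysis can be derived from the reasons for hospitalisation in Table 2, the serious adverse event reports and the hospital admission information collected for the health economics. The sponsor should confirm that reasons are recorded for every admission, since the Table 2 row is worded around OHSS-related ones.

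The cost is one extra analysis, a few more records for adjudication, and a little noise from unrelated admissions (power about 85–88% with a 2–5% equal background). The sample size and the interim rule do not change.

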### Follow-up

Data will be collected as follows:

Participant diary data, self-completed daily until symptom resolution.Monitoring visits, either face to face or remotely, at days 7, 14, 21 and 28 or until symptoms have resolved.Symptom resolution visit, face to face (unless symptoms resolve during hospitalisation and the data can be collected from medical notes or the participant).A symptom deterioration visit, to assess if hospitalisation may be required.A participant self-completed questionnaire at 28 days.Remote follow-up at day 90, to collect ongoing pregnancies/pregnancy outcome (eg, miscarriage), thrombosis/embolism and significant infections. Participants not pregnant at this time point will be considered complete and will not require further data collection.For participants identified as pregnant at 90 days, live birth and pregnancy outcome (eg, miscarriage) as well as neonatal death, congenital abnormalities and SAEs for the baby at 13.5 months.

### Safety considerations, safety monitoring and AE reporting

All AEs and SAEs will be recorded at each participating fertility unit. All AEs/SAEs will be followed up until satisfactory resolution or until the treating clinician and the principal investigator deems the event to be chronic or the participant to be stable. Clinical/research staff will ask participants for any details of AEs at each daily contact in the intervention arm and then in both groups at all time points.

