For time to resolution of OHSS assessed within 28 days postrandomisation, Kaplan-Meier curves will be used to visualise the resolution curves between treatment arms and differences qualified using a log-rank test. Median time to resolution by treatment arm with 95% CI will be calculated and reported as summary measures of within-group effects. Participants who fail to achieve resolution of symptoms within 28 days postrandomisation will be censored. Sensitivity analysis and alternative approaches when the proportional hazard assumption is not met will be detailed in the SAP.

For cumulative length of OHSS hospital stay, bootstrapping resampling procedure (accounting for stratification) will be used to obtain the median difference with 95% CI and associated p value. For patient satisfaction at 28 days, a total satisfaction score will be analysed using a mixed effects linear regression model adjusted for site (as a random effect) and OHSS severity (as a fixed effect), and the adjusted mean difference between treatment arms with 95% CI and associated p value will be presented.

Analysis of safety outcomes (eg, AEs and SAEs) will be based on descriptive statistics using the safety analysis population defined based on treatment-as-received population. Details of additional analysis accounting for repeated events and differential follow-up is found in the SAP.

Subgroup analyse will be performed to explore whether there is heterogeneity in treatment effect on the primary outcome across the following prespecified subgroups:

Baseline severity of OHSS (moderate or severe).Whether a participant is taking a preventative drug at randomisation (yes or no).Whether the participant has early or late OHSS at randomisation.Whether the OP procedure was done vaginally or abdominally. For participants who received multiple procedure (which may happen in few cases), this classification will be based on the first performed procedure.

A mixed effects logistic regression model that includes an interaction effect between preplanned subgroup and treatment group adjusted for site (as a random effect) and severity of OHSS (as a fixed effect) only if it is not a subgroup factor of interest will be used.

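### Adverse events are asked about daily in the outpatient paracentesis arm but less often in usual care, so non-serious AEs to day 28 are not comparably ascertained

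*Protocol article*

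**What the plan says.** In the protocol article, under Safety considerations, safety monitoring and AE reporting, staff are to "ask participants for any details of AEs at each daily contact in the intervention arm and then in both groups at all time points".

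Table 2 (Outcomes) agrees. It has an AE entry by telephone in the column for daily collection until symptom resolution, with the footnote "This will only be possible for participants who are being contacted daily" and then "When they are not being contacted daily it will be asked at every contact". It also shows AE collection at the weekly time points (outpatient or medical notes), at symptom resolution, at symptom deterioration and during hospitalisation, for both arms.

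The Follow-up section sets the shared schedule: "Monitoring visits, either face to face or remotely, at days 7, 14, 21 and 28 or until symptoms have resolved".

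Intervention and control treats the daily diary differently by arm. In OP, "This information will be used by the clinical team in the intervention arm on a daily basis to inform further management". In UC, "these data will be sent directly to CTRU for input into the database and will not be available to be reviewed by site staff".

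The outcome concerned is the listed secondary outcome "AEs within 28 days of randomisation", which serves the stated objective of establishing the safety of OP. The Statistical analysis section says: "Analysis of safety outcomes (eg, AEs and SAEs) will be based on descriptive statistics", in a population defined by treatment received. It leaves to the SAP further analysis that allows for repeated events and for follow-up that differs between participants.

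**The concern.** How often a woman is asked affects how many minor events are recorded. A short episode of pain or nausea is likely to be mentioned the next day and may be forgotten or thought not worth mentioning at a visit several days later. OP women have two daily routes to a recorded AE that UC women lack: the daily question, and staff sight of a diary covering vomiting, pain and shortness of breath.

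The trial is open label. Its stated safeguard against assessment bias, blinded adjudication, covers hospitalisation and not AEs. An excess of minor AEs in OP could then be harm from the procedure, better detection, or both. This is a fixed rule of data collection, so an SAP cannot fully repair it: analysis cannot recover UC events that nobody asked about.

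**Working it through.** **1. Number of occasions on which a woman is asked.** For a woman symptomatic throughout the 28 days, the Table 2 schedule gives:
- OP: up to about 28 days with an AE question, plus the common contacts.
- UC: 4 scheduled visits, plus any deterioration, inpatient, resolution or other contact.

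**2. What the documents supply for sizing.** They give no AE rate and no detection figure. The only design figure used below is 112 per arm. It reproduces: with 41% v 21%, one-sided 2.5% and 90% power, n = [1.96√(2×0.31×0.69) + 1.2816√(0.41×0.59 + 0.21×0.79)]² / 0.20² = 110.3, so 111 per arm against the stated 112. Nothing here questions that sample size.

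**3. Assumed model A: recall decays with time.** Let the chance of reporting an event d days after onset be exp(−kd), with k = ln 2 / half-life. Daily asking has a mean delay of 0.5 day. Weekly asking has delays of 0.5, 1.5, …, 6.5 days, equally likely. With r = exp(−k), the recorded OP:UC ratio at equal true rates is 7 / (1 + r + … + r⁶):
- half-life 14 days: 7 / 6.06 = 1.15
- half-life 7 days: 7 / 5.30 = 1.32
- half-life 3 days: 7 / 3.89 = 1.80

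**4. Assumed model B: fixed detection probabilities.** Recorded rate = true risk × detection, with detection 0.95 in OP and 112 per arm. At a true risk of 40% in both arms:

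| UC detection | Recorded OP v UC | Ratio | Spurious excess | Chance of nominal two-sided p<0.05 |
|---|---|---|---|---|
| 0.95 | 38% v 38% | 1.00 | 0 points | 5% |
| 0.85 | 38% v 34% | 1.12 | 4 points | 10% |
| 0.75 | 38% v 30% | 1.27 | 8 points | 25% |
| 0.60 | 38% v 24% | 1.58 | 14 points | 63% |

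For the third row, SE = √[(0.38×0.62 + 0.30×0.70)/112] = 0.063, so 0.08/0.063 = 1.27 and the chance is Φ(1.27 − 1.96) ≈ 25%. At a true risk of 20% the last three excesses are 2, 4 and 7 points; at 60% they are 6, 12 and 21 points. The plan is descriptive for AEs, so the last column only gauges how misleading a table could look.

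**5. What is not in these models.** Model A treats UC as asked weekly and nothing more. Extra UC contacts, events still present at the next visit, and medical notes all pull the ratio towards 1. Earlier resolution in OP would shorten daily asking. At the design rates about 0.41×112 = 46 UC women would be admitted against 0.21×112 = 24 in OP, and AEs are collected from inpatients, which adds detection in UC. Grouping by treatment received would also place any UC woman who has paracentesis outside her randomised arm.

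**The case against.** The strongest reply is that daily contact belongs to the OP strategy. Asking about AEs at a contact already taking place is ordinary safety practice, and calling UC women daily would alter a pragmatic comparator. That stands, and it is why the fix leaves the contact schedule alone.

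Second, UC is not confined to weekly questions. The footnote has every participant asked at every contact, and Table 2 adds resolution, deterioration and inpatient contacts. A reader might infer seven questions a week against one; the documents do not support that as the typical contrast. It is an extreme case.

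Third, the net direction is not certain. Faster resolution in OP and more admissions in UC work the other way. This is why the verdict says probably.

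Fourth, a reader might infer that the trial cannot establish the safety of OP at all, or that no AE excess in OP could be interpreted. The documents do not support this. Thrombosis, embolism and significant infection at day 90, and pregnancy and neonatal outcomes at 13.5 months, are collected from medical notes on one schedule for both arms. SAEs, such as those leading to admission, depend little on how often a woman is asked. A bias against OP is also conservative for a claim that OP is safe, although it could equally make a safe procedure look harmful or hide a true difference among detection effects.

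Fifth, the SAP is not shown and may handle this. Its announced scope, repeated events and unequal follow-up, does not plainly cover frequency of asking within the same follow-up, but that cannot be settled from the article.

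**Conclusion.** The asymmetry is stated in the safety section and confirmed by Table 2; it is not inferred from silence. It leaves non-serious, self-reported AEs to day 28 without comparable ascertainment, most likely to the disadvantage of OP. The size cannot be computed from the documents. A recorded ratio of about 1.1 to 1.8 at equal true rates covers both illustrations, and both rest on unsourced assumptions about recall or detection. The primary outcome, SAEs and the later outcomes are largely untouched. The point deserves a change while recruitment continues, because a stated objective and a listed secondary outcome depend on this comparison and the remedy is cheap.

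**What to change.** Keep the daily OP safety contacts and add three things.

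1. At each common contact (days 7, 14, 21, 28, resolution, deterioration, hospitalisation), ask both arms the same AE question covering the whole interval since the last common contact, whether or not an event is already logged.
2. Record on the CRF every contact at which each AE was reported.
3. Base the between-arm comparison of non-serious AEs on the common-contact answers, together with all SAEs. Still report all AEs by arm, list separately those found only at OP daily contacts, and describe these as not comparable.

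A simpler filter, keeping only AEs first reported at a common contact, should be avoided. An event already logged at an OP daily call would drop out, while the same event in UC would wait for the visit and count. Under model A, with events spread evenly over the week, about 1 in 7 OP events would remain, and the OP:UC ratio at equal true rates would be 1.15/7 = 0.16, 1.32/7 = 0.19 or 1.80/7 = 0.26: a large bias in favour of OP.

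The cost is a repeated question at common contacts, one CRF field, SAP wording, and some mild OP events shown outside the comparative table. Women whose 28 days have already passed cannot be asked again; for them only the separate listing, where the contact was recorded, and the caveat are available.
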